## 4 Background

### 4.1 Existing research

Management of newly diagnosed T1D in children and adolescents is challenging for patients, families, carers, and health care professionals. Glucose is the dominant metabolic substrate for brain function (1) and the glycaemic instability inherent in T1D is known to affect brain structure and function in those with poorly controlled disease (2). Severe hypoglycaemia, particularly nocturnal episodes, is more common in children (3) and has a negative impact on the developing brain (2; 4). Fear of hypoglycaemia is common (5), impacts quality of life and psychological well-being of the young and their families (6), and leads to suboptimal glucose control (6). Glycaemic control usually deteriorates during adolescence. The Diabetes Control and Complications Trial (DCCT) revealed both higher HbA1c levels and a 50% increase in the rate of severe hypoglycaemia in intensively treated adolescents compared to adults (7). Teenagers with T1D face the burden of diabetes management in addition to major physiological and psychological changes accompanying puberty.

#### 4.1.1 Preservation of C-peptide – evidence and approach

At the clinical diagnosis of diabetes most patients have residual pancreatic islet cells which can continue to secrete insulin for several additional years. In the DCCT (7), 35% of participants with diabetes duration of 1-5 years had persistent islet cell function (meal stimulated C-peptide levels of 0.2 to 0.5 pmol/ml). Assignment to the intensively managed group reduced the risk for loss of C-peptide by 57% over the mean 6.5 years of study. This was very clear proof that metabolic control had a significant effect on preservation of islet cell function. However, intensification of insulin therapy inevitably hits the barrier of hypoglycaemia (8). Four in five youth aged 13 to 18 years fails to meet the International Society for Pediatric and Adolescent Diabetes (ISPAD) glycaemic control target of HbA1c below 7.5% (58.5 mmol/mol) (9).

In the DCCT, those who had greater or equal 0.20 pmol/ml C-peptide initially or sustained over a year had markedly less complications – a 79% decrease in the relative risk of retinopathy (10). Importantly, these benefits were seen in the face of less hypoglycaemia events. Individuals in the intensive treated group with  $\geq 0.20$  pmol/ml C-peptide had about the same frequency of severe hypoglycaemia as those in the standard care group; a 30% reduction as compared to those in intensive therapy without this level of C-peptide. A more recent analysis found a linear relationship between frequency of retinopathy progression and C-peptide as low as 0.03 pmol/ml (11).

Islet transplant studies have also shown that even small amounts of residual beta-cell function are clinically important. Vantyghem et al. showed that while significant beta-cell function was required to improve mean glucose, lower glucose excursions, and result in insulin independence, participants who maintained minimal beta-cell function experienced almost no severe hypoglycaemic events (12).

Metabolic control following the onset of type 1 diabetes can have a major impact on preserving residual islet cell function. Two weeks of islet cell rest after clinical diagnosis of diabetes resulted in stimulated C-peptide levels 1 year post diagnosis of 0.51 pmol/ml (13), greater than that seen after a year of cyclosporine treatment (peak C-peptide of 0.45 pmol/ml (14). However, a short four day burst of tight glucose control failed to improve meal stimulated C-peptide secretion 12 months post diagnosis (15).

#### **4.1.2 Closed loop technology**

The emergence of new technologies including continuous glucose monitoring (16), sensor augmented pump therapy (SAP) (17), and threshold pump suspend (18; 19) provides new opportunities to improve outcomes. The most promising approach is closed loop insulin therapy (20) which combines real-time continuous glucose monitoring with insulin pump therapy to achieve glucose responsive subcutaneous insulin delivery mimicking beta-cell function. The vital component of such a system, also known as an artificial pancreas (AP), is a computer-based algorithm. The role of the control algorithm is to translate, in real-time, the information it receives from the CGM and to compute the amount of insulin to be delivered by the pump. The other components include a real-time continuous glucose monitor and an infusion pump to titrate and deliver insulin. Timely insulin delivery is expected to rest the beta-cells and lessen the immune attack.

The closed loop approach has been successfully evaluated in children and adolescents in controlled laboratory studies (21-23) and in home settings (24-27). Investigations in adults have also been conducted (25; 28; 29). The results demonstrated improved glucose control and reduced risk of hypoglycaemia events. Psychosocial assessments supported acceptability and positive impact of this novel therapeutic approach among children/adolescents and carers (30), although the potential benefit in preserving cognitive function is, as yet, unknown. The closed loop approach promises to transform management of type 1 providing a tangible option to improve residual beta-cell function.

## 4.2 Artificial Pancreas research at Cambridge

### 4.2.1 Preclinical testing of Cambridge closed loop algorithm

The research conducted at the University of Cambridge focused on developing a closed loop system for overnight glucose (initial approach) and day-and-night control (more recent applications; see below) in subjects with T1D. Studies that have been performed employed model predictive control (MPC) – this algorithm estimates user-specific parameters from CGM measurements taken every 1 to 15 minutes and makes predictions of glucose excursions, which are then used to direct insulin infusion between meals and overnight whilst standard bolus calculator is used to deliver prandial insulin (31).

The MPC algorithm has been studied extensively using *in silico* testing utilising a simulator developed by members of the study team (32). The simulations suggested a reduced risk of nocturnal hypoglycaemia and hyperglycaemia with the use of the MPC algorithm (33).

### 4.2.2 Studies of closed loop in children and adolescents with type 1 diabetes in the clinical research facility

To date around sixty children and adolescents with type 1 diabetes have been studied at the clinical research facility. Closed loop insulin delivery was maintained on more than 100 nights. No episodes of significant hypoglycaemia (plasma glucose concentration less than 2.8 mmol/l) have been observed thus far during closed loop blood glucose control. Results from these studies were published in The Lancet (21) and showed that overnight closed loop therapy increased the time spent euglycaemic by 37% and reduced the risk of overnight hypoglycaemia eight-fold, as compared to conventional pump treatment. Different real-life scenarios predisposing to nocturnal hypoglycaemia, such as afternoon exercise, were explored and closed loop therapy reduced the risk of overnight hypoglycaemia as compared to conventional insulin pump therapy in a randomised, cross-over design.

### 4.2.3 Studies of closed loop in adults with type 1 diabetes in the clinical research facility

We have completed two randomised overnight closed loop studies in 24 adults with T1D, testing a similar closed loop system comprising CGM and pump devices and the MPC algorithm. The first study (n=12) assessed the feasibility and efficacy of overnight closed loop insulin delivery following a moderate-sized (60g carbohydrate) evening meal compared with conventional pump therapy. We demonstrated that overnight closed loop insulin delivery, compared with usual continuous subcutaneous insulin infusion (CSII), significantly increased time in target plasma glucose range

(3.9-8 mmol/l) by 24% and reduced glycaemic variability as measured by standard deviation of plasma glucose. The improvements in glucose control seen on closed loop were even greater after midnight, when time in target increased by 41%. In the second study we tested the efficacy of overnight closed loop following a common situation such as consuming a large (100g carbohydrate) evening meal and drinking alcohol (0.75g ethanol/kg body weight of 13%abv white wine). We showed that overnight closed loop insulin delivery, compared with conventional CSII, similarly increased time in target plasma glucose between 3.9 and 8.0 mmol/l by 24% and reduced time spent above target by 11%, even following such challenges. Importantly these improvements during closed loop were achieved with no increased requirement in the average rate of insulin infusion overnight. These results have been published in the British Medical Journal (34).

#### **4.2.4 Overnight closed loop study in children and adolescents with type 1 diabetes in home setting**

Following successful demonstration of safety and efficacy of closed loop insulin delivery in the research facility, overnight closed loop studies under free living conditions were commenced in July 2012. The first study compared the efficacy and safety of closed loop with sensor augmented pump therapy in 16 adolescents over a three week duration (24). Closed loop was activated over at least 4 hours on 269 nights (80%); sensor data were collected over at least 4 hours on 282 control nights (84%). Closed loop increased the time when glucose was in target range by a median 15% (interquartile range -9 to +43),  $P < 0.001$ . Mean overnight glucose was reduced by a mean  $0.8 \pm 3.2$  mmol/l,  $P < 0.001$ . Time when glucose was below 3.9 mmol/l was low in both groups but nights with glucose below 3.5mmol/l for at least 20min were less frequent during closed loop (10% vs. 17%,  $P = 0.01$ ). Despite lower total daily insulin doses by a median 2.3 (interquartile range -4.7 to +9.3) units,  $P = 0.009$ , overall 24h glucose was reduced by a mean 0.5 (standard deviation 2.3 mmol/l ( $P = 0.006$ ) during closed loop.

In a second multicentre, crossover, randomised, controlled study, we compared 12 week use of an overnight closed loop insulin delivery system with sensor augmented pump therapy in children and adolescents aged 6 to 18 years (25). The proportion of time with the night-time glucose level in the target range (3.9 to 8.0 mmol/l) was higher during the closed loop phase than during the control phase (by 24.7 percentage points; 95% CI, 20.6 to 28.7;  $P < 0.001$ ), and the mean night-time glucose level was lower (difference, -1.6 mmol/l; 95% CI, -2.2 to -1.1;  $P < 0.001$ ). The area under the curve for the period in which the day-and-night glucose levels were less than 3.5 mmol/l was lower by 42% (95% CI, 4 to 65;  $P = 0.03$ ). Two severe hypoglycaemic episodes occurred during the closed loop phase when the closed loop system was not in use.

#### 4.2.5 Overnight closed loop studies in adults with type 1 diabetes in home setting

A four week overnight closed loop study under free living conditions in 24 adults with type 1 diabetes on insulin pump therapy in a multicentre crossover study design was completed in 2014 (29). Closed loop was utilised over median 8.3 (interquartile range 6.0, 9.6) hours on 555 nights (86%). The proportion of time when overnight glucose was in the overnight target range between 3.9 and 8.0 mmol/l from midnight to 07:00 was significantly higher during closed loop compared to sensor augmented pump therapy ( $52.6\% \pm 10.6$  vs.  $39.1\% \pm 12.8$ , mean  $\pm$  SD;  $p < 0.001$ ). Mean overnight glucose ( $8.2 \pm 0.9$  vs.  $9.0 \pm 1.3$  mmol/l,  $p = 0.005$ ) and time spent above target ( $44.3\% \pm 11.9$  vs.  $57.1\% \pm 15.6$ ,  $p = 0.001$ ) were significantly lower during closed loop. Time spent below target was low and comparable between interventions [ $1.8\%$  (0.6, 3.6) vs.  $2.1\%$  (0.7, 3.9),  $p = 0.28$ ].

#### 4.2.6 Day-and-night closed loop studies in adolescents with type 1 diabetes in home setting

We completed a randomised, crossover design study in adolescents aged 10 to 18 years who underwent two 7-day home periods of sensor-augmented insulin pump therapy or closed loop insulin delivery without supervision or remote monitoring (27). The proportion of time when the sensor glucose level was in the target range (3.9–10 mmol/L) was increased during closed loop insulin delivery compared with sensor-augmented pump therapy (72% vs. 53%,  $P < 0.001$ ; primary end point), the mean glucose concentration was lowered (8.7 vs. 10.1 mmol/L,  $P = 0.028$ ), and the time spent above the target level was reduced ( $P = 0.005$ ) without changing the total daily insulin amount ( $P = 0.55$ ). The time spent in the hypoglycaemic range was low and comparable between interventions. A three week single centre study in children and adolescents has also been completed ( $N = 12$ ).

#### 4.2.7 Day and night closed loop studies in adults with type 1 diabetes in home setting

In 2014, we completed a first study testing a day and night home system over a seven day period in 17 adults. This randomised clinical trial adopted a multicentre, multi-national, crossover design. During the home phase, the percentage time when glucose was in target range (3.9 to 10.0 mmol/l) was significantly higher during closed loop compared to sensor augmented pump therapy (75 [61, 79] vs. 62 [53, 70]%, median [IQR],  $p = 0.005$ ). Mean glucose (8.1 vs. 8.8 mmol/l,  $p = 0.027$ ) and time spent above target ( $p = 0.013$ ) were lower during closed loop while time spent below target was comparable ( $p = 0.339$ ). Increased time in target was observed during both day-time ( $p = 0.017$ ) and night-time ( $p = 0.013$ ).

We completed a multicentre, multinational, crossover, randomised, controlled study under free living home conditions comparing 24/7 closed loop insulin delivery with sensor augmented pump therapy

(control intervention) in 33 adults with type 1 diabetes (25). The proportion of time that the glucose level was in the target range (3.9 to 10.0 mmol/l) was 11.0 percentage points (95% confidence interval [CI], 8.1 to 13.8) greater with the use of the closed loop system day and night than with control therapy ( $P<0.001$ ). The mean glucose level was lower during the closed loop phase than during the control phase (difference,  $-0.6$  mmol/l; 95% CI,  $-0.9$  to  $-0.3$ ;  $P<0.001$ ), as were the area under the curve for the period when the glucose level was less than 3.5 mmol/l (39% lower; 95% CI, 24 to 51;  $P<0.001$ ) and the mean glycated hemoglobin level (difference,  $-0.3\%$ ; 95% CI,  $-0.5$  to  $-0.1$ ;  $P = 0.002$ ).

### 4.3 Risk and benefits

A potential key benefit of closed loop insulin delivery is the retention of residual C-peptide secretion which has been shown to decrease the risk of microvascular complications and a lower risk of severe hypoglycaemia by 65% when compared to intensively treated participants without residual beta-cell function in the DCCT trial (7). Thus the most important long term impact of improved glucose control and residual islet function may be reduced rates of diabetes complications and improved quality of life.

Any potential risks presented by this investigation have been minimized and adequate testing, safeguards, and safety monitoring will be incorporated into the investigation to further minimize and mitigate these risks. A detailed Risk Management File adopting risk management processes complying with EN ISO 14971:2012 Medical Devices – Application of Risk Management to Medical Devices, will be submitted as part of the regulatory submission to the MHRA.

### 4.4 Rationale for the current study

The study builds on recent technological advances of closed loop insulin delivery (artificial pancreas). The purpose of this study is to test the impact of continued intensive metabolic control using closed loop insulin delivery after diagnosis on preservation of C-peptide residual secretion. The study enrolls children aged 10 and older, as they are characterised by higher residual C-peptide secretion at diagnosis compared to younger children. The present study will also test the feasibility and acceptance of this therapy so that it could be considered as a standard treatment modality in the future.

We propose an internal pilot to test the feasibility of recruiting a patient cohort within a predetermined time period.

The extension phase will allow ongoing assessment of the impact of continued intensive metabolic control using closed-loop insulin delivery on residual C-peptide and will test acceptability of this therapy over a longer duration.

#### 4.5 Automated closed loop system (FlorenceM) to be used in the present study

The automated closed loop system (FlorenceM) will consist of:

- Next generation sensor augmented Medtronic insulin pump 640G (Medtronic Minimed, CA, USA) incorporating the Medtronic Enlite 3 family real time CGM and glucose suspend feature
- An Android smartphone containing the Cambridge model predictive algorithm and communicating wirelessly with the insulin pump using a proprietary translator device.

An overview of this proposed automated closed loop system is given in Figure 1.

**Figure 1: Representative design of the proposed FlorenceM automated closed loop system**

[figure not shown]

## 4.6 Follow up closed-loop platform (CamAPS FX) to be used in the present study

Participants in the closed-loop arm can use the follow up closed-loop platform any time after recruitment into the study. The automated closed-loop platform (CamAPS FX) will consist of:

- Dana insulin pump (Diabecare, Sooil, Seoul, South Korea)
- Dexcom G6 real-time CGM sensor (Dexcom, Northridge, CA, USA)
- An Android smartphone hosting CamAPS FX Application with the Cambridge model predictive control algorithm and communicating wirelessly with the insulin pump
- Cloud upload system to monitor CGM/insulin data.

An overview of this proposed automated closed loop platform is given in Figure 1A.

[figure not shown]

Figure 1A CamAPS FX comprises Samsung Galaxy phone (or similar) running Cambridge control algorithm, Dana insulin pump (Sooil), G6 real-time CGM sensor (Dexcom).

## 5 Objectives

### 5.1 Primary objective

The primary objective is to evaluate the effect of continued intensive metabolic control using closed loop insulin delivery after diagnosis on preservation of C-peptide residual secretion by comparing the area under the stimulated C-peptide curve (AUC) of a mixed meal glucose tolerance test conducted at the 12 month visit in participants receiving closed loop insulin delivery with those receiving standard therapy, i.e. multiple daily injections applying basal bolus regimen.

The objective of an internal pilot phase is to carry out preliminary evaluation of recruitment, randomisation, treatment and follow-up assessments at the five participating sites.

### 5.2 Secondary objectives

#### 5.2.1 Glucose control

The objective is to examine the efficacy of day-and-night closed loop compared with standard basal bolus regimen as far as glucose control is concerned. We will compare between group differences in HbA1c, and parameters based on subcutaneous continuous glucose monitoring (CGM), such as the percentage of time spent within, below and above the target range from 3.9 to 10.0 mmol/l.

#### 5.2.2 Safety

The objective is to evaluate the safety of day and night automated closed loop glucose control in terms of episodes of severe hypoglycaemia and other adverse events.

#### 5.2.3 Utility

The objective is to determine the frequency and duration of use of the automated closed loop system.

#### 5.2.4 Human factors

The objective is to assess cognitive, emotional, and behavioural characteristics of participating subjects and family members and their response to the closed loop system and clinical trial in order to aid interpretation of trial results and inform recommendations for future use of closed loop systems.

### 5.2.5 Health economics

A cost utility analysis on the benefits of closed loop insulin delivery will be conducted to inform reimbursement decision-making.

## 5.3 Extension Phase objectives

The objective of the extension phase is to evaluate the effect of continued intensive metabolic control using closed loop insulin delivery after diagnosis on preservation of C-peptide residual secretion by comparing the fasting C-peptide and glucose levels conducted at the 36 and 48 month visit in participants receiving closed loop insulin delivery with those receiving standard therapy, i.e. multiple daily injections.

The extension phase will also examine the efficacy of day-and-night closed loop compared with standard basal bolus regimen on glucose control comparing between group differences in HbA1c, and parameters based on subcutaneous continuous glucose monitoring (CGM).

The safety of day and night automated closed loop glucose control will be evaluated in terms of episodes of severe hypoglycaemia and other adverse events.

The frequency and duration of use of the automated closed loop system will be assessed.

Emotional and behavioural characteristics of participating subjects and family members and their response to the closed loop system and clinical trial will be evaluated using questionnaires.

## 6 Study design

This will be an open-label, multi-centre, randomised, single-period, two-arm parallel group study with internal pilot phase, contrasting automated closed loop glucose control (CL) with multiple daily injections (MDI).

At diagnosis of T1D young people and families will be invited to participate in the study. Eligible participants will be randomised in a 1:1 ratio using central randomisation software to either closed loop (CL) or multiple daily injection therapy (MDI). The study will aim for a total of 96 (15-20 per site) completed participants. Recruitment will target up to 190 to allow for dropouts. Subjects who have signed the consent/assent but drop out during run-in may be replaced. The study flow chart is outlined in Figure 2.

There will be an optional 24 month extension phase for participants in both study arms to continue with the treatment allocated at randomisation.

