### 3 Summary

The purpose of the study is to use a novel treatment approach, the artificial pancreas, after diagnosis of type 1 diabetes (T1D) to improve glucose control with the anticipated improvements of residual C-peptide secretion.

This is an open-label, multi-centre, single-period, randomised, parallel group design study. It is expected that a total of up to 190 subjects (aiming for 96 randomised subjects) will be recruited within 21 days of diagnosis of type 1 diabetes through paediatric diabetes centres in the UK. Half of the participants aged 10 to 16.9 years will be treated by conventional insulin injections and the other half by the artificial pancreas (closed loop insulin delivery system). Each treatment will last 24 months. All participants completing the 24 month study period will be invited to continue in an optional extension phase with the treatment allocated at randomisation for a further 24 months.

Subjects in the intervention group will receive additional training on components of the artificial pancreas, i.e. insulin pump and continuous glucose monitoring (CGM), prior to starting closed loop insulin delivery. Subjects in the control intervention group will continue with standard therapy, i.e. multiple daily injection therapy. The study includes up to 14 visits and 1 telephone/email contact for subjects completing the study. After run-in and randomisation, visits will be conducted every 3 months in both arms. Beta-cell function will be assessed by serial measurement of C-peptide in response to a standardised mixed meal tolerance test (MMTT). MMTTs will be conducted at baseline, 6-, 12- and 24 months post diagnosis.

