# 7 Study subjects

## 7.1 Study population

This is a multicentre study and recruitment will take place at the following centres:

1. Addenbrooke's Hospital, Cambridge, UK
2. Leeds Teaching Hospital, Leeds, UK
3. Alder Hey Children's Hospital, Liverpool, UK
4. Nottingham Hospital, Nottingham, UK
5. Oxford Children's Hospital, Oxford, UK
6. Southampton Children's Hospital, Southampton, UK
7. Royal Hospital for Children and Yong People, Edinburgh, UK

Up to a total of 96 youths aged 10 to 16.9 years will be recruited within 21 days of diagnosis of type 1 diabetes. Each site will aim to recruit between 15 to 20 participants. Participants may also be recruited from other diabetes centres (Patient Identification Centres) in the East Anglia region and London for the Addenbrooke's site, from the Thames Valley region for the Oxford Children's Hospital site and from the Wessex Paediatric Network for the Southampton Children's Hospital site.

Potential participants will be identified by their treating clinicians and a contact with the research team will be established if agreed. Study information leaflets and/or similar recruitment material will be handed out or sent to participants by the research team including an invitation to join the study. Written informed consent will be obtained from all participants aged 16 years and parents/guardians of participants aged 15 years and younger, before any study related activities. Participants aged 15 years and younger will be asked to provide evidence of their assent to the study procedures.

At 24 months, all participants opting to continue with the extension phase of the study will be asked to re-consent. Written informed consent will be obtained from participants aged 16 years and parents/guardians of participants aged 15 years and younger, before any study related activities. Participants aged 15 years and younger will be asked to provide evidence of their assent to the study procedures.

**Figure 2: Study flow chart**[figure not shown]

Figure 3: Study flow chart for extension phase

[figure not shown]

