## 14.7 Sample size and power calculations

The primary analysis will compare the difference between groups in the levels of the 2-hour AUC-mean using the  $\ln(\text{mean C-peptide}+1)$ . The residual standard deviation of the  $\ln(x+1)$  transformed C-peptide AUC analysis of covariance is referred to by TrialNet (Lachin 2011) as the root mean squared error (RMSE). The back-transform,  $\exp(y) - 1$ , of the mean of the transformed values is referred to by TrialNet as the geometric-like mean. In the DirecNet/TrialNet new onset studies (Lachin 2011), the point estimate for RMSE was 0.18 (transformed scale) and was used in the power calculations. As in the TrialNet sample size calculations, a 50% improvement was assumed in the geometric-like mean C-peptide AUC. The sample size depends on the geometric-like mean value in the control group. The original TrialNet sample size calculations assumed a value of 0.37 pmol/ml for the control group based on the lower 90% confidence limit from previous data (Lachin 2011). The present power calculation applied the same value. A 50% increase in the intervention group of the geometric-like mean C-peptide AUC gives  $0.37 \times 1.50 = 0.555 \text{ pmol/ml}$ . After  $\ln(x+1)$  transformation, the mean values in the control and treatment groups are 0.315 and 0.441 (transformed scale), respectively, the treatment effect is  $0.441 - 0.315 = 0.126$ . The treatment effect of 0.126 with a standard deviation of 0.18 requires 44 subjects per group at 90% power for a two sided-test at the 0.05 level. Allowing for 10% loss to follow up means we would need a total of 96 randomised participants (48 per group).

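### The enrolment target of 96 is given as randomised, completed or recruited participants in different sections; a one-participant-per-group rounding slip in the dropout inflation comes with it

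*Combined protocol and SAP*

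**What the plan says.** **96 randomised.** Protocol 14.7 derives the size. It states "The treatment effect of 0.126 with a standard deviation of 0.18", and that this "requires 44 subjects per group at 90% power for a two sided-test at the 0.05 level". It then concludes: "Allowing for 10% loss to follow up means we would need a total of 96 randomised participants (48 per group". SAP 3 repeats the calculation, and the synopsis gives 96 randomised, 48 per group. Protocol 3 expects "up to 190 subjects (aiming for 96 randomised subjects", and Protocol 6.2 has all 96 randomised subjects followed to study completion.

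**96 completed.** Protocol 6: "The study will aim for a total of 96 (15-20 per site) completed participants". The same paragraph puts recruitment at up to 190 to cover dropouts and allows people who drop out during run-in to be replaced.

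**At most 96 recruited.** Protocol 7.1: "Up to a total of 96 youths aged 10 to 16.9 years will be recruited within 21 days of diagnosis". That section lists seven centres and asks each for 15 to 20 participants.

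**Up to 190 recruited.** Protocol 3, Protocol 6 and SAP 5.1.

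**The concern.** Recruited, randomised and completed are separate stages in this trial. Participants consent, go through baseline assessment and run-in, are randomised, and are then followed for 24 months. The same number cannot describe all three stages once any loss is allowed for. Someone working from section 6 or 7.1 alone would take a different enrolment target from someone working from 14.7, and the final report needs one planned number against which to describe achieved enrolment.

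The second, smaller matter is that the stated 90% power belongs to 44 evaluable participants per group, and 48 randomised per group does not leave 44 after the 10% loss that the plan assumes.

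**Working it through.** **Inputs** (Protocol 14.7; SAP 3 agrees on the effect, SD, alpha, power and loss): effect 0.126 and SD 0.18 on the ln(x+1) scale, the SD being explained by "the point estimate for RMSE was 0.18 (transformed scale"; two-sided alpha 0.05; power 90%; loss 10%. Allocation is 1:1 (Protocol 6).

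**Reproducing the plan's 44 per group**
- Effect: ln(1.555) − ln(1.37) = 0.4415 − 0.3148 = 0.1267, stated as 0.126.
- Normal approximation: n = 2 × [0.18 × (1.960 + 1.282) / 0.126]² = 42.9, so 43 per group.
- Exact two-sample t-test (noncentral t): 44 per group. The plan's figure is reproduced, and the unrounded effect gives the same 43 and 44.

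**Inflating for 10% loss**
- From 44: 44/0.90 = 48.9, so 49 per group, 98 in total. Multiplying instead, 44 × 1.10 = 48.4, also rounds up to 49.
- From 43: 43/0.90 = 47.8, so 48 per group, 96 in total. The stated 96 therefore follows from the normal-approximation 43, not from the stated 44.
- In reverse: 48 × 0.90 = 43.2 per group. Loss can reach only 1 − 44/48 = 8.3% before a group falls below 44.

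**Power for effect 0.126 and SD 0.18 (noncentral t)**

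| Evaluable per group | Alpha 0.05 | Alpha 0.04 |
|---|---|---|
| 43 | 89.4% | 87.5% |
| 43.2 | 89.5% | 87.7% |
| 44 | 90.1% | 88.3% |
| 48 | 92.4% | 90.9% |

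The 0.04 column is shown because SAP 13 tests the primary outcome at that level, while SAP 6.2 and Protocol 14.5 use 5%.

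**Comparing the three targets**
- 96 randomised: 96 × 0.90 = 86.4 evaluable, 43.2 per group.
- 96 completed: 96/0.90 = 106.7, about 107 randomised (108 if each group is rounded up, since 48/0.90 = 53.3 gives 54). That is 11 or 12 more than 14.7.
- At most 96 recruited: this cannot stand beside up to 190 recruited.

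**Per-site range**
- Seven sites: 7 × 15 = 105 to 7 × 20 = 140, all above 96.
- Five sites, the number still named for the pilot in Protocol 5.1 and 6.1: 75 to 100, which does span 96.
- An average of 96 randomised over seven sites is 96/7 = 13.7.

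**The case against.** The best defence is that the intended number is not in real doubt. Both sample size sections, the synopsis, the summary and section 6.2 agree on 96 randomised. Section 6 states an aim, not a rule for ending enrolment, and 7.1 probably uses recruited loosely for randomised. Read literally, 96 completed would raise power, so it is no threat. That settles which number to keep. It does not remove the conflict, because the plan separates recruitment from randomisation elsewhere and both outlying statements are in current text.

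The inflation slip is one participant per group and about 0.6 percentage points of power. SAP 5.1 puts all randomised participants in the primary analysis, and SAP 6.3.1 uses earlier C-peptide values by direct likelihood when the 12-month value is missing, so a lost participant is not simply removed. This stands: the slip is rounding and should not be presented as a loss of power that matters.

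A reader might infer from 7.1 that a cap of 96 recruits would leave far fewer than 96 randomised and so an underpowered trial. The documents do not support this. It needs a rate of randomisation among recruits, and none is stated: 190 is only ever a ceiling. It also needs the cap to be literal, which the 105 to 140 implied by the seven sites in the same section contradicts.

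Finally, Protocol 22 plans first inclusion in August 2016, up to 2.5 years of enrolment, and last completion of the 24-month study in June 2021. On that timetable enrolment would have ended by about mid-2019, before version 8.0 of 10 September 2019. The practical value is then mostly in reporting the planned size correctly.

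**Conclusion.** The enrolment target is stated inconsistently, and sections 6 and 7.1 are the ones out of line with 96 randomised. Section 6 implies about 107 randomised at 10% loss. Section 7.1 conflicts with up to 190 recruits elsewhere and with its own sites. This is a correction of an internal inconsistency that should be made; it is not evidence that the trial is too small.

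The rounding point is minor. With 96 randomised and 10% loss, about 43 per group are evaluable. Power is about 89% at two-sided 0.05, or about 87.5% at 0.04. These figures assume effect 0.126, SD 0.18, equal loss in both groups, and no information recovered from participants without a 12-month value. The choice of alpha costs more (89.4% to 87.5% at 43 per group, 1.9 points) than the rounding (90.1% to 89.5%, 0.6 points), so power cannot be restated properly until the alpha is settled.

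**What to change.** 1. Protocol 6: replace the completed target with 96 randomised.
2. Protocol 7.1: state up to 190 recruited, aiming for 96 randomised.
3. Protocol 6, Protocol 7.1 and the synopsis: reconcile the 15 to 20 per site with seven sites, and say whether it counts recruited or randomised participants.
4. Protocol 14.7 and SAP 3: say that 96 randomised with 10% loss is expected to leave about 43 evaluable per group. Give power of about 89% if the primary test is at two-sided 0.05, or about 87.5% if it is at 0.04. Quote only the figure for the alpha confirmed after SAP 6.2, SAP 13 and Protocol 14.5 have been reconciled. Writing in 89% at 0.05 without that step would contradict SAP 13.

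The cost is wording only. No participants are added and no procedure or endpoint changes; the stated power becomes slightly less favourable.
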